### Data management plan

Collected data will be entered into the pre-designed SPSS file (Version 21) and then checked, cleaned and recoded where needed. Only the authorized personnel will be able to access data to avoid any potential manipulation. Data set will be archived and only available on request once the study is over.

### Statistical analysis plan

Descriptive analysis: Socio-demographic data of the participants e.g. gender, parental occupation, parental education status, family history of NCDs, family living standard will be obtained for both intervention and control school. All categorical variables will be summarized in frequency and percentages and continuous variables in mean and standard deviation. To estimate the association of these characteristics of intervention and control group, t-tests and chi-square tests will be done.

Inferential analysis: To estimate the efficacy of the intervention, before-after data will be analyzed and paired t-test and McNemar’s chi-square tests will be done in this regard. Also, comparison will be done between the intervention and control group for pre and post-intervention status of knowledge, attitude and practices.

Association analysis: Binary regression analysis will be done to estimate the association between socio-demographic variables with changes in the outcome variables- knowledge, attitude, and practice for both groups. Also, to estimate the association of knowledge score and attitude with the change in self-reported practices, regression analysis will be done.

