## Methodology

### Study design and setting

A before-after designed intervention study will be conducted in two randomly selected secondary schools in a semi-urban area of Dhaka, capital of Bangladesh. One school will be selected randomly as intervention school and the other one as control school. Possibility of diffusion of intervention contents among students from one school to another will be minimized by selecting the schools at a reasonable distance.

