### Participant recruitment and data collection

The study will follow a fixed study design (Additional file 1). Sample size is determined based on a previous study where a mean difference of BMI was found 1.48 between intervention and non-intervention adolescent groups after 3-months of motivational interview [23]. Expecting a similar difference, calculated sample size is 274 in each group considering effect size (E) = 1.48; standard deviation (S) = 5.98; standardized effect size (E/S) = .25; significance level, α (two-sided) = 0.05; β = 1- power = 0.2, non-response rate = 5%]. A complete list of grade-ten students will be prepared after collecting their class roll and batch number from the administrative offices of the selected schools. All the students of grade-ten will be invited to participate in the study through announcement and personal contact prior to the date of data collection.

At first, a baseline survey will be conducted among the grade ten students of both schools by a pre-tested questionnaire to attain their current status of knowledge, attitude and practices related to NCDs. Then, students from the intervention school who reported at least two NCDs risk behaviors will be invited to participate in a health education session through phone call to their parents. Selected students who will present at the day of intervention will be considered having implied consent from their parents and will be enrolled in the intervention group up to the attainment of the required sample size. Enrolled students will be given intervention through health education session. Students with any kind of physical disability or limited movement will be excluded from the study. Students from the control group will receive a one-hour session on carrier guidance. Students will be kept blind about the intervention they received. After 3 months of the baseline survey, a post-intervention survey will be conducted among the participants from both intervention and control group using the same questionnaire.

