### Reporting of the result

It is decided to disseminate this intervention and the findings of the proposed study through a dissemination seminar and through reporting on it. The Transparent Reporting of Evaluations with Non-randomized Designs (TREND) statement checklist will be followed while reporting this study to ensure maintaining highest standard and getting maximum possible benefit out of this study in creating evidences.

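### The efficacy comparison states no adjustment for the socio-demographic variables collected in both schools or for the baseline outcome, and baseline significance tests do not fill that gap

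*Protocol article*

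**What the plan says.** All of the analysis wording is in the Statistical analysis plan section of the protocol article.

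- **Variables collected.** The descriptive paragraph lists: "gender, parental occupation, parental education status, family history of NCDs, family living standard will be obtained for both intervention and control school".
- **Baseline differences.** They are handled by testing: "To estimate the association of these characteristics of intervention and control group, t-tests and chi-square tests will be done". Nothing is said about what follows from a significant or a non-significant result.
- **Efficacy.** The inferential paragraph names paired t-tests and McNemar tests on before-after data, and adds: "Also, comparison will be done between the intervention and control group for pre and post-intervention status of knowledge, attitude and practices". It names no model, covariate or baseline adjustment for that comparison.
- **Regression.** The association paragraph relates socio-demographic variables to changes in knowledge, attitude and practice in both groups. It mentions neither a group term nor an adjusted intervention effect.

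On design, the Study design and setting section says: "One school will be selected randomly as intervention school and the other one as control school". The Reporting of the result section classes the study as non-randomised: "The Transparent Reporting of Evaluations with Non-randomized Designs (TREND) statement checklist will be followed while reporting this study". The recruitment section states the requirement of at least two risk behaviours for the intervention school only.

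**The concern.** Drawing lots between two schools decides which one gets the intervention. It does not balance the pupils, because each arm is a single school with whatever mix of families it serves. If a characteristic such as parental education is related to knowledge or diet and differs between the schools, the difference in end-line status contains that characteristic's contribution as well as any intervention effect.

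A baseline p-value does not repair this. It removes no bias. A non-significant value does not show balance, and a significant one leads to no stated step. The variables needed to reduce the problem are already to be collected and already enter a regression, but not one described as estimating the intervention effect. At stake is whether a difference between the schools at end-line can be read even partly as an effect of the sessions.

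**Working it through.** **1. The plan's own sample size.** Inputs from the recruitment section: "effect size (E) = 1.48; standard deviation (S) = 5.98; standardized effect size (E/S) = .25" and "significance level, α (two-sided) = 0.05; β = 1- power = 0.2, non-response rate = 5"%; result "calculated sample size is 274 in each group".

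- n per group = 2 × (1.96 + 0.8416)² / (1.48/5.98)² = 15.70 / 0.06125 = 256.3, so 257.
- Allowing for 5% non-response: 257 / 0.95 = 271.
- The stated 274 is within 3% of this, so it is not disputed.
- Analysed per school: 274 × 0.95 ≈ 260, used below.

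**2. What the baseline tests can detect.** Two-proportion test, two-sided 0.05, 260 per school. Power ≈ Φ(|p1 − p2|/SE − 1.96), with SE = √[(p1(1−p1) + p2(1−p2))/260]. The 50% starting value is an assumption.

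| Imbalance | SE | Power | Missed |
|---|---|---|---|
| 50% v 58% | 0.0436 | 45% | 55% |
| 50% v 60% | 0.0434 | 63% | 37% |
| 50% v 70% | 0.0421 | 99.7% | 0.3% |

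For a continuous characteristic, SE = √(2/260) = 0.0877 SD. An imbalance of 0.1 SD is declared significant 21% of the time and one of 0.2 SD 63% of the time. Moderate imbalance is often missed. Large imbalance is found, but the plan attaches no consequence to finding it.

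**3. Bias in an unadjusted comparison of post status.** For a binary characteristic, bias = (difference in prevalence) × (effect of the characteristic on the outcome, in SD). The document gives neither factor, so both are assumed over a range. The last column gives the chance that a two-sided z-test with SE 0.0877 SD is significant when the intervention has no effect.

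| Imbalance | Covariate effect | Bias | False positives |
|---|---|---|---|
| 10 points | 0.1 SD | 0.01 SD | 5.1% |
| 10 points | 0.5 SD | 0.05 SD | 8.8% |
| 20 points | 0.1 SD | 0.02 SD | 5.6% |
| 20 points | 0.5 SD | 0.10 SD | 20.7% |

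The range therefore runs from negligible to material. These rates reflect the measured covariate only and ignore any other school effect.

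**4. Whether adjustment works.** One scenario was simulated: 3,000 runs, 260 per group, no true effect, and a continuous covariate with an assumed 0.3 SD imbalance and an assumed correlation of 0.5 with the outcome. The unadjusted comparison had a bias of 0.149 SD and 39.6% false positives. With the covariate in the model, the bias was −0.002 SD and false positives were 4.8%. This covariate was the only confounder and was measured without error, so the result shows the mechanism and does not predict this trial.

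**The case against.** **The text is silent rather than opposed to adjustment.** The sentence on comparing the groups names no method, and an article may leave a covariate list to a fuller plan. This stands in part. A reader might infer that the variables will never be adjusted for, and the document does not say so. But its analysis section does name the baseline tests, the efficacy tests and the regressions, and it places the socio-demographic variables in the first and last of these only. As written, following it yields no adjusted intervention effect.

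**The variables are not only significance-tested.** Correct: they also enter the association regression. The wording about both groups fits separate models or a pooled one. Neither reading states a group effect, so the regression does not serve as the adjusted comparison.

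**Paired tests cancel stable differences between schools.** This stands for change within pupils. A reader might infer that confounding enters every efficacy analysis at full strength. It does not: the bias in the working applies to the comparison of post status. Looking at pre status as well would reveal baseline outcome differences. However, no between-group comparison of change is stated, and a within-school change alone is not an intervention-control contrast.

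**The size is unknown.** This stands. It is tempting to divide 0.05 or 0.10 SD by the planned 0.25 SD. But 0.25 is 1.48/5.98 for BMI, while the comparison at issue concerns knowledge, attitude and practices, for which no planned effect is given. Nor do the documents show that the schools will differ. They are in one semi-urban area and one grade is surveyed, so imbalance is plausible but of unknown size. Several imbalances could add up or offset one another.

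**Adjustment does not cure the design.** This also stands and limits what the remedy can claim.

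**Conclusion.** The point holds as an improvement to the stated analysis. The plan gives the efficacy comparison no adjustment for five characteristics it collects or for the baseline outcome, in a one-school-per-arm study that it classes as non-randomised itself. Measured differences between the schools can therefore bias the comparison of post-intervention status. The baseline tests miss a 10-point imbalance about 37% of the time at 260 per school, and they trigger nothing when they succeed.

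The bias could be anywhere from 0.01 to 0.10 SD under the assumed imbalances of 10 to 20 points and covariate effects of 0.1 to 0.5 SD. The document supports no single figure. Nor does it support the view that covariate adjustment would make the schools comparable. School and intervention coincide, and the risk-behaviour criterion is stated for one school only, so unmeasured differences between schools remain inseparable from the intervention.

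**What to change.** In the inferential paragraph, define the efficacy estimate as a regression of the end-line outcome on group, linear for scores and measurements and logistic for practices. Adjust for the same outcome at baseline and for gender, parental occupation, parental education, family living standard and family history of NCDs. Include all five whatever their baseline p-values. Report adjusted and unadjusted estimates with 95% CIs. For logistic models, note that adjusted and unadjusted odds ratios can differ even without confounding.

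Add a sentence stating that, with one school per arm and the two-risk-behaviour criterion stated only for the intervention school, adjustment reduces measured confounding but cannot separate the intervention from unmeasured school differences.

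Replacing the baseline tests with standardised differences is an optional reporting change.

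The cost is a few sentences and a few lines of code on data already planned for collection, plus a simple rule for pupils with a missing covariate. Fixing the covariate set in advance also prevents its being chosen by baseline p-value or by result.

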### Specific objectives

To conduct a baseline survey to evaluate the knowledge, attitude and practices about NCD risk behaviours such as unhealthy diet, physical inactivity, smoking etc. among the respondents.To develop a health education intervention based on the baseline survey to reduce NCDs related behavioural risk factors among adolescents.To apply the health education intervention to the target group through effective communication approach and tools.To conduct a post interventional survey with the same questionnaire used in baseline data collection.To evaluate the intervention by comparing pre and post intervention data.

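### Efficacy is assigned to within-group paired t-tests and McNemar tests; the control school enters only an added, unspecified comparison that states no contrast of change

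*Protocol article*

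**What the plan says.** Under Statistical analysis plan, the inferential paragraph names the method for efficacy: "To estimate the efficacy of the intervention, before-after data will be analyzed and paired t-test", with McNemar's test named alongside it for the same purpose. The next sentence adds a second analysis: "Also, comparison will be done between the intervention and control group for pre and post-intervention status of knowledge, attitude and practices". It gives no test or model and no contrast of change between groups.

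Four other places bear on this:

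- Specific objectives describes the evaluation as follows: "To evaluate the intervention by comparing pre and post intervention data".
- Study design and setting puts one school in each arm: "One school will be selected randomly as intervention school and the other one as control school".
- Participant recruitment and data collection selects the intervention group on baseline behaviour: "students from the intervention school who reported at least two NCDs risk behaviors will be invited to participate in a health education session". No such criterion is stated for control students. Of the end line it says: "a post-intervention survey will be conducted among the participants from both intervention and control group using the same questionnaire".
- The same section bases the sample size on a BMI difference between intervention and non-intervention groups: 1.48 with SD 5.98, two-sided alpha 0.05, power 80%, non-response 5%, giving 274 per group.

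**The concern.** A paired t-test or a McNemar test asks whether students in one group changed. It does not ask whether they changed more than students who did not receive the intervention. Anything that moves answers over three months is counted as effect: familiarity with a questionnaire given twice, season, age, school teaching, and regression to the mean.

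Regression to the mean follows from the plan's own enrolment rule. Intervention students are chosen because they reported at least two risk behaviours at baseline, and self-reported behaviours of this kind are outcomes under Practice. Some of those reports will reverse by chance at the second survey. In a McNemar test the reversals look like improvement.

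A concurrent control school is surveyed at both times, and its purpose is to take out such influences. The test designated for efficacy does not use it for that.

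**Working it through.** **1. The plan's own sample size is a between-group size.** Inputs from Participant recruitment and data collection: difference 1.48, SD 5.98, two-sided alpha 0.05, power 0.80, non-response 5%.

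- n per group = 2 × (1.960 + 0.842)² × (5.98/1.48)² = 2 × 7.849 × 16.33 ≈ 256.3, so 257. Then 257/0.95 = 270.5, so 271. The stated 274 is within 3% of this.
- A paired test at the same standardized effect (1.48/5.98 = 0.2475) would need about 130 students. The study is therefore sized for a two-group contrast that the designated efficacy tests do not make.
- Evaluable per group: 274 × 0.95 = 260.3, taken as 260 below.

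**2. Paired t-test when the intervention does nothing.** Let both schools drift by g baseline SDs, with pre-post correlation ρ. The documents give neither value, so both are assumptions. The SE of the mean change is √(2(1−ρ)/260), and z = g/SE. The rejection rate is Φ(z − 1.96) + Φ(−z − 1.96). At ρ = 0.5 the SE is √(1/260) = 0.0620.

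| Drift g (SD) | z | Rejection rate |
|---|---|---|
| 0 | 0 | 5% |
| 0.05 | 0.81 | 13% |
| 0.10 | 1.61 | 36% |
| 0.15 | 2.42 | 68% |
| 0.20 | 3.22 | 90% |
| 0.25 | 4.03 | 98% |

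Over ρ = 0.3 to 0.7 the rate is 10–18% at 0.05 SD, 28–55% at 0.10 SD and 78–99% at 0.20 SD. The true difference between schools in change is zero in every row.

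**3. McNemar test after selection on baseline behaviour.** This was simulated with no drift and no effect. Assumptions: four independent binary behaviours of equal prevalence, latent test-retest correlation 0.5 or 0.7, and 260 students with at least two behaviours at baseline. The test was applied to one behaviour.

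| Prevalence | Apparent fall from regression alone | Rejection, selected | Rejection, no selection |
|---|---|---|---|
| 30% | 14–18 points | over 99% | about 5% |
| 50% | 7–9 points | 61–74% | about 5% |
| 70% | 2–3 points | 13–16% | about 5% |

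The distortion shrinks as behaviours become more common, because the filter then excludes fewer students.

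**4. What a between-group analysis costs in power.** Inputs: 260 per group, difference 1.48, SD 5.98, student-level variance only, assumed ρ = 0.3 / 0.5 / 0.7. The effective SD is S for end line only, S√(1−ρ²) for ANCOVA and S√(2(1−ρ)) for change scores.

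- End line only: 80.6% throughout.
- ANCOVA: 84% / 90% / 98%.
- Difference in change scores: 67% / 81% / 95%.

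Clustering by school is not included. With one school per arm it cannot be estimated.

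**The case against.** The strongest reply is the sentence that follows the efficacy sentence. A comparison of intervention and control groups is planned, and controls are surveyed at both times. A reader might infer that the control school goes unused; the protocol does not support that. What stands is narrower: the control school is not in the test designated for efficacy, and the comparison it does enter states no contrast of change.

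Four more limits are fair:

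- A reader might take the added comparison to be two separate cross-sectional tests. The text does not say so. Its model is open, and a separate analysis plan could specify it. That would not change the efficacy sentence, which makes a positive choice of method.
- A reader might infer that the plan would declare success on the paired tests alone. No success rule is stated, and the between-group results would be available beside them.
- The pre/post wording in Specific objectives does not exclude a comparison with controls, so it is weak support.
- Nothing in the documents shows that scores will rise on retest after three months. Drift is an assumption, which is why the range above starts at zero.

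**Conclusion.** The point holds in this form: the analysis designated for efficacy is within-group, so it cannot separate an intervention effect from change that would have happened anyway. With 260 students, correlation 0.5 and no effect, the false-positive rate of the paired t-test goes from 5% at zero drift to 13% at 0.05 SD, 36% at 0.10 SD and 98% at 0.25 SD. For practices, the enrolment rule alone can raise the McNemar rate well above 5% with no drift, by an amount that depends strongly on how common the behaviours are. Drift, correlation, prevalence and reliability are all assumed. The direction of the fault does not depend on them, but its size does.

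A reader might also infer that a between-group model would make the efficacy test valid. It would not do so alone. If filtered intervention students are compared with unfiltered controls, regression to the mean stays differential. With one school per arm, any difference between the schools remains confounded with the intervention under every model.

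**What to change.** Reword the inferential paragraph before end line data are analysed:

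- Make the efficacy analysis the between-group difference at end line adjusted for the baseline value of the same outcome: ANCOVA for knowledge and attitude scores, and a logistic or log-binomial model for each practice.
- Fix this one estimand in advance. A group-by-time interaction is not an equivalent alternative: when the schools differ at baseline the two estimate different quantities and can disagree.
- Apply the at-least-two-behaviours criterion to control students in the analysis as well, using their baseline survey.
- Keep the paired t-test and McNemar results as descriptive, by school.
- State that one school per arm leaves school and intervention effects confounded, and limit the efficacy conclusion accordingly.

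No new data are needed, and at student level baseline adjustment does not lower power for a given group size (84–98% against 80.6% under the assumptions above). The real cost is that the filter may shrink the control group by an amount the documents do not allow one to estimate. The number of eligible control students should be counted from the baseline survey and power restated.

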### Quality control measurement

Quality of the data and adherence with the protocol will be ensured by a quality control panel consisting of four senior physicians from Bangabandhu Sheikh Mujib Medical University (BSMMU).

The facilitators to deliver the intervention will be practicing physician who will have experiences on individual patient counseling. Selected facilitators will be trained on the intervention by written dialogues addressing the sequential framework of the intervention model in a 5-days workshop. Then they will have to perform dry run. Their lectures will be recorded and then scrutinized to ensure standard and similarity between the lectures. A supervisor team consisting of a psychologist, a child health specialist, a public health specialist and a nutritionist will be present during the dry run and at the actual intervention session to ensure the quality. All the sessions will be audio-recorded to measure the quality of the intervention and to confirm its reproducibility. A SPIRIT checklist has been filled up for this protocol to ensure its standard (Additional file 3).

